**Figure 1 figure1:**
[figure not shown]
Draft avatar editor system showing a sample character that can transition from masculine to feminine gender expression.

**Figure 2 figure2:**
[figure not shown]
Draft scene of opposite sex and same sex flirtation.

**Figure 3 figure3:**
[figure not shown]
Draft HIV risk screen adapted from the Centers for Disease Control and Prevention risk estimator tool.

**Figure 4 figure4:**
[figure not shown]
HIV prevention services locator based on publicly available the Centers for Disease Control and Prevention locators.

### Formative Focus Groups

Focus groups will occur in 2 rounds (n=32 each) and will be conducted by [name], DG, and BW, who have experience with qualitative research used to develop behavioral interventions. Focus group participants will be recruited via advertisements placed on various social media sites (eg, Facebook, Snapchat, and Instagram). Interested participants will be directed to a web-based eligibility screener in the REDCap (Research Electronic Data Capture) platform, a secure Health Insurance Portability and Accountability Act (HIPAA)–compliant web application designed exclusively to support data capture for research studies [34], to determine their age, gender, sexual behaviors and orientation, and state of residence. Eligibility will also be confirmed by the project staff via phone. Those eligible and interested will be sent a link to survey in REDCap, with the consent and assent forms embedded, meant to collect information on youth sociodemographics, use of games and social media, knowledge of HIV and PrEP, sexual risk behaviors, and experiences with HIV testing and PrEP use. Eligible and interested participants will also provide information on the date and time of the focus. Focus groups will be stratified by sexual orientation (heterosexual vs lesbian, gay, bisexual, transgender, queer or questioning, and others [LGBTQ+]), and age (13-17 years vs 18-24 years). Before the focus groups, the research staff will review the consent and assent forms with participants and obtain verbal consent and assent before proceeding with the focus group.

Focus group questions cover the following topics: HIV and PrEP knowledge, perceptions and experiences regarding HIV testing, current use of and access to gaming technology (eg, use of smartphones, game consoles), perceptions regarding game enhancements and their potential role in increasing HIV testing and access to PrEP, perceptions about the role of social media and its influence on HIV testing behaviors, and opinions regarding effective recruitment approaches through social media. The enhanced life-simulation game will be demonstrated to participants, and feedback will be elicited regarding the acceptability and relevance of characters, texts, actions, and graphics, as they relate to race, culture, and structural factors. Following the focus group, participants will be sent the link to a survey in REDCap to assess their change in knowledge of HIV and PrEP as well as their satisfaction with the game prototype.

All focus groups will be audio recorded, and a verbatim transcription is professionally produced. The resulting text file will be entered into the qualitative data analysis software Atlas.ti 7.0 (ATLAS.ti Scientific Software Development GmbH) and analyzed using an a priori and open coding process aimed at identifying relevant themes and categories to inform the development of the game modifications for round 2 focus group testing as well as the final game prototype in the pilot test. Key decisions will include potential differences by age and sexual orientation, the types of games, art styles, social features, type or frequency of in-game bonuses, and responses of different kinds of in-game virtual rewards for actions such as demonstrating knowledge of HIV risks and virally spreading the game to peers. Game modifications will be made based on the initial focus group feedback (n=32), after which the second group of participants (n=32) will be recruited and shown the revised game. Survey data will be cleaned, downloaded, and exported into Excel or SAS files, and descriptive statistics will be analyzed. Pre- and postgame knowledge levels will be calculated; however, because of the small sample size, no statistical testing will be performed.

### Pilot Test

#### Finalization of Game Prototype

If it is determined that AYA in the formative focus group does not like the enhanced life-simulation game, additional modifications will be made. Once the look and feel have been finalized, the game production team will implement v2.0, creating base code, audio, and 3D art or animation using the Unity *middleware* engine.

#### User Field Testing

Pilot test participants will be recruited via advertisements placed on various social media sites. Interested participants will be directed to a web-based eligibility screener in REDCap. Participant eligibility will be confirmed by the project staff via phone. Eligible participants will provide electronic consent and assent and complete the baseline survey electronically via a HIPAA-compliant participant management database. Participants will then be sent the gaming app electronically to download on their phone and will have unlimited access for 1 month. User pilot testing will allow project staff to identify any unanticipated issues with game log-ins, navigation, functionality, paradata collection, or other unforeseen technical issues. During user testing, game use as well as HIV testing and PrEP locator use will be monitored and paradata will be accessed for a 1-month period.

We will also pilot the use of the HIPAA-compliant participant management database for participant screening, survey collection, and data management and troubleshoot for any issues with phone connectivity, data caching, paradata collection, or other potential issues. Baseline data on HIV testing and knowledge will be collected to preliminarily describe the anticipated characteristics of our web-based sample. Measures of game satisfaction [35], usability [36], and a modified version of the motivation, attitude, knowledge, and engagement instrument [37] will also be piloted to determine how well the game addresses HIV knowledge and testing. At the end of the 1-month period, brief surveys and in-depth interviews (IDIs) will be conducted with the 10 pilot participants to elicit features of the games that worked well and identify those that might prohibit full use of the intervention.

Survey data will be cleaned, downloaded, and exported into Excel or SAS files. Given the small sample size and objectives of this study, quantitative analysis will be primarily descriptive to measure usability, acceptability, and satisfaction as well as to confirm baseline characteristics and behaviors of our intended study population. All interviews will be audio recorded, and verbatim transcription professionally produced. The resulting text file will be entered into the qualitative data analysis software Atlas.ti 7.0 and analyzed using an a priori and open coding process aimed at identifying potential barriers and facilitators to use. Critical and essential modifications will be made to the game, paradata, and HIPAA-compliant data management platforms before the RCT.

### Randomized Controlled Trial

#### Overview

We will evaluate the impact of the life-simulation game compared with app-based HIV educational materials in an RCT with 300 AYAs. To enroll a sample representative of diverse racial or ethnic and sexual behaviors as well as a sample of non–clinic-attending AYAs, recruitment will occur primarily through social media. We will place targeted advertisements toward YMSM and Black and Hispanic AYAs on social media sites, such as Facebook, Instagram, and Snapchat. In addition, we will provide recruitment materials with quick response codes to the DC Health and Montgomery county school-based health programs. Interested AYAs will click on an advertisement and be directed to a web-based eligibility screener to determine their age, gender, sexual behaviors and orientation, state of residence, and availability of a reliable cell phone. The eligibility of the participants will be confirmed by the project staff via phone. Eligible participants will then provide electronic consent and complete the baseline survey electronically. Participants will be randomized using the block randomization method designed to ensure groups of equal sample sizes (1:1). Participants will be randomized in blocks of 6, stratified by age (13-17 years and 18-24 years) and sexual behavior (LGBTQ+ vs heterosexual), using a random number generator for assignment. Randomization will occur through the HIPAA-compliant participant management database platform. We will compare conditions on HIV testing, knowledge, risk behaviors, and PrEP access at enrollment and at 1, 3, and 6 months post enrollment via electronic survey assessments. At 6 months, a subset of intervention participants (n=25) will participate in in-depth *exit* interviews regarding their experience being in the study. A schematic of the study design is shown in Figure 5.

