#### Intervention Delivery

Intervention participants will have access to the full revised study game for 3 months from the time of enrollment and will be able to play the game and have up to 30 hours of content available. To sustain interest and engagement over the study period and maximize potential efficacy, new downloadable game content will be available every 4 weeks post enrollment through the 3-month follow-up.

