#### Control Condition

Before rolling out the RCT, we will develop an app that will include basic information on HIV (eg, routes of transmission, data on the epidemiology of HIV among youth, prevention information, and information on HIV testing and PrEP) as well as a link to the HIV risk estimator and HIV testing and PrEP locators. Participants assigned to the control arm will receive a link to download this informational app containing this content and will have unlimited access to the app for a 3-month period.

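### A single published block size of 6 within four strata would let anyone who sees earlier assignments deduce up to about a quarter of the allocations; randomly varied block sizes avoid this cheaply

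*Protocol article*

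**What the plan says.** The Overview of the Randomized Controlled Trial section describes a "block randomization method designed to ensure groups of equal sample sizes (1:1") and gives one block size: "Participants will be randomized in blocks of 6, stratified by age (13-17 years and 18-24 years) and sexual behavior (LGBTQ+ vs heterosexual"). That makes 2 × 2 = 4 strata.

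The same section sets the order of events. Applicants complete a web screener that records, among other items, age and sexual orientation. Then "The eligibility of the participants will be confirmed by the project staff via phone". Next, "Eligible participants will then provide electronic consent and complete the baseline survey electronically". Assignment follows, using a random number generator: "Randomization will occur through the HIPAA-compliant participant management database platform".

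The arms receive visibly different products. Under Intervention Delivery, "Intervention participants will have access to the full revised study game for 3 months from the time of enrollment". Under Control Condition, "Participants assigned to the control arm will receive a link to download this informational app".

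The article does not say whether the staff who make the eligibility calls can see earlier assignments, or who or what sends the product links.

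**The concern.** Concealment fails if someone who influences entry can work out the next assignment. Hiding the list inside a database does not prevent this when three conditions meet: the block size is known, past assignments can be recognised, and the next participant's stratum is known. Here the block size is in print, the product identifies the arm, and the screener supplies both stratification factors before the call. Once three participants in a block have gone to one arm, the rest of that block is determined.

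What would be at stake is comparability of the arms. The primary outcome is self-reported HIV testing, compared at 6 months with a chi-square test. That test does not adjust for baseline differences, so an imbalance created at entry would carry into the result.

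**Working it through.** The article gives no figure for predictability, so there is none to reproduce.

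**Inputs.** From the Overview: block size 6, ratio 1:1 (three places per arm), four strata. Sample size 300, from Statistical Analysis. Assumed, not in the article: an observer who knows the block size and every earlier assignment in the stratum.

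**Step 1: certain assignments in a complete block.** There are C(6,3) = 20 equally likely orders. An assignment is certain once one arm has used its three places.

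- Positions 1 to 3: never certain.
- Position 4: the first three are alike in 2 of 20 orders, 0.10.
- Position 5: one arm has three of the first four in 8 of 20 orders, 0.40.
- Position 6: always certain, 1.00.

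Expected number certain = 0.10 + 0.40 + 1.00 = 1.5. The general formula for a block of 2m, 2m/(m+1), gives 6/4 = 1.5 with m = 3. The share is 1.5/6 = 25%.

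**Step 2: incomplete last blocks.** With 75 participants in each stratum there are 12 complete blocks and 3 left over, none of them certain. The share is 12 × 1.5 / 75 = 18/75 = 24.0%, or 4 × 18 = 72 of 300. Simulation with random stratum sizes, in equal or unequal proportions, gives about 24.3%, or 0.243 × 300 ≈ 73.

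**Step 3: best guess.** Always guessing the arm with more places left is right with probability 0.5, 0.6, 0.6, 0.7, 0.7 and 1.0 at positions 1 to 6. The mean is 4.1/6 = 68.3%, against 50% by chance.

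**Step 4: delay between call and assignment.** Steps 1 and 2 measure certainty at the moment of assignment, but any influence would act at the call. As an illustration (the article gives no lag), suppose others in the stratum have been called but not yet assigned, and are assigned first.

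- One pending: (0.10 + 0.40)/6 = 8.3% certain at the call.
- Two pending: 0.10/6 = 1.7%.
- Three pending: none.

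**Step 5: alternatives.** All are judged against an observer who knows all earlier assignments and the block size, or the set of sizes.

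| Scheme | Certain | Best guess |
|---|---|---|
| Fixed 6, complete blocks | 25% | 68.3% |
| Fixed 8, complete blocks | 20% | 66.6% |
| Fixed 10, complete blocks | 16.7% | 65.3% |
| Fixed 6, 75 per stratum (simulated) | about 24% | about 68% |
| Random 4/6/8, 75 per stratum (simulated) | about 2% | about 68% |

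Varying the size nearly removes certainty. It does not reduce the best-guess rate.

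**The case against.** The strongest objection is that the route to bias is not shown. A reader might infer that a quarter of the assignments are in fact known in advance, or that the people who make the calls also send the links and watch the sequence. The article supports neither. It says only that project staff confirm eligibility, that the platform assigns, and that control participants receive a link. The order of events also works against prediction: the participant completes consent and the baseline survey after the call, so assignments need not follow the order of calls, and step 4 shows how quickly certainty falls with even one person pending. The entry criteria are largely facts the applicant has already entered in the screener, and no assessment of motivation at the call is described. This part of the objection stands. It makes the quarter a conditional upper bound.

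A second objection is that list generation, masking of callers and concealment within the platform are details an article may leave to the full protocol. That also stands, and their absence is not criticised here. Confirming eligibility before assignment is already the stated order.

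Neither objection reaches the block size. It is stated, single and published, and use of a database does not prevent deduction from assignments already seen.

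**Conclusion.** The fixed block size of 6 is an avoidable weakness in a stated design choice. It is not an internal contradiction, nor evidence that selection bias will occur. Its size is at most 25% of assignments per complete block, about 24% (72 to 73 of 300) once incomplete blocks are counted. That figure rests on three assumptions: the eligibility staff know the block size, they can see every earlier assignment in the stratum, and they can place the next participant in the sequence. The article confirms none of these for the callers beyond publishing the size. Any delay between call and assignment lowers the figure.

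**What to change.** In the Overview, replace the single block size with randomly varying block sizes, for example 4, 6 and 8 in random order, within the same four strata. State that the sizes are not disclosed to staff who confirm eligibility, and leave them out of public documents until enrolment ends.

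Because the best-guess rate does not improve, the change should go alongside keeping earlier assignments from those staff. If the full protocol already provides for that, nothing more is needed on that side. Simply enlarging a fixed block is a weaker remedy, as the table shows.

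The cost is one randomization setting and one protocol sentence before the first RCT participant. The article was written before the RCT began, and its Pilot Test section already foresees changes to the data management platform beforehand. The statistical price is small: the largest possible within-stratum imbalance rises from 3 (half of 6) to 4 (half of 8).

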**Figure 5 figure5:**
[figure not shown]
Aim 3 study flow diagram. DC: District of Columbia; REDCap: Research Electronic Data Capture.

#### Intervention Delivery

Intervention participants will have access to the full revised study game for 3 months from the time of enrollment and will be able to play the game and have up to 30 hours of content available. To sustain interest and engagement over the study period and maximize potential efficacy, new downloadable game content will be available every 4 weeks post enrollment through the 3-month follow-up.

#### Control Condition

Before rolling out the RCT, we will develop an app that will include basic information on HIV (eg, routes of transmission, data on the epidemiology of HIV among youth, prevention information, and information on HIV testing and PrEP) as well as a link to the HIV risk estimator and HIV testing and PrEP locators. Participants assigned to the control arm will receive a link to download this informational app containing this content and will have unlimited access to the app for a 3-month period.

#### Measures

Electronic surveys via REDCap will be used to assess the behavior at baseline and at 1, 3, and 6 months post enrollment, as it is confidential and allows for complex branching or skip patterns [34]. Participants will be emailed the REDCap surveys 7 days before their designated completion date, on their completion date, and 7 days after their completion date if not completed. Standard items will be administered to gather demographic data (including age, educational level, sexual orientation, socioeconomic status, race, and ethnicity). Surveys will collect information on the following validated domains: HIV- and PrEP-related knowledge; self-reported sexual and HIV risk behaviors; self-perceived risk for HIV; perceived norms; barriers to HIV testing; reported HIV testing and PrEP uptake; behavioral intentions including intent to test for HIV; seeking PrEP; and reducing risky behaviors, self-efficacy, and game use, interest, acceptability, and usability.

At 6 months, a purposely selected subset of intervention participants (n=25) will participate in IDIs regarding their experience being in the study. The IDIs will be conducted by trained qualitative interviewers and will follow semistructured interview guides. The IDIs will assess the extent to which app components facilitate or inhibit HIV testing. Central to the IDIs will be understanding the participants’ use of the app. To obtain a range of perspectives, we will seek feedback from participants stratified by sexual behaviors (heterosexual vs LGBTQ+), age group (13-17 years vs 18-24 years), whether they sought and received HIV testing, and levels of game play and locator use based on the paradata (none, low-moderate, and high use).

### Outcomes

#### Primary Outcomes

The primary outcome measure for the study is HIV testing. This will be measured as self-reported HIV testing in the past 6 months. For all participants who report testing, we will attempt to validate reported testing by eliciting a description of the HIV testing process and requesting that a secure photo of their test results be sent to study staff to minimize social desirability bias. We will compare self-reported HIV testing between the 2 groups at 6 months.

#### Secondary Outcomes

As self-reported measures tend to overestimate HIV testing and given the age range of our participants and potential structural barriers to the receipt of HIV testing among AYAs (eg, parental knowledge of testing, lack of transportation, inconvenient clinic times), a secondary outcome will be intent to test for HIV. The intent to test will be assessed using a validated 6-point Likert scale [38], shown to be predictive of future testing behavior, with responses ranging from *very unlikely* to *extremely likely* to test in response to the question. “how likely are you to get tested in the next 6 months?” We will dichotomize this score into *extremely likely* versus other. Other secondary outcomes will use previously published questions and validated scales (Table 1) and include changes in (1) HIV knowledge [39]; (2) risk perception [40] and behaviors (eg, condomless sex); (3) PrEP knowledge [41,42], screening [41,42], and uptake (also verified with a photograph of a pill bottle or prescription); (4) risk estimator scores and locator (HIV and PrEP) use; and (5) game acceptability [35] and usability [36], including frequency and duration of use, and reasons for continued or discontinued use.

**Table 1 table1:** Measures planned for each phase.

Domain			Assessment time		
			Focus group	Pilot test	RCT^a^

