### Statistical Analysis

In our pilot study [33], we found that approximately 10% of sexually active AYAs reported being tested for HIV in the past 4-6 months. A sample of approximately 300 subjects (150 per arm) would achieve >80% power to detect a moderate effect corresponding to a difference of at least 13 percentage points (equivalent to a relative risk of 2.3 assuming a 10% prevalence of HIV testing in the past 4-6 months in the control group) in HIV testing between the intervention and control groups after 6 months using a two-sided test at a 5% significance level and assuming a 16% attrition rate after 6 months. All data will be inspected for inaccurate input (eg, out-of-range values, implausible means, and variation). We will first summarize the outcome measures descriptively overall and within each intervention arm at each time point. We will make every effort to obtain all data. Any patterns of missingness will be investigated and reported. Sensitivity analyses, including rerunning analyses with imputed values for missing data, will be conducted to assess the impact of missingness on the study findings.

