All primary analyses will be conducted using an intent-to-treat approach. The primary analysis will focus on differences between the treatment and control groups at the 6-month follow-up visit using a chi-square test for independence (the outcome will be taken as having had an affirmative response on the outcome measure during the 6-month study period). We will also investigate the differences between the rates of HIV testing in the treatment and control groups, stratifying by age (13-17 years vs 18-24 years) and sexual orientation (LGBTQ+ vs heterosexual identity). We will perform a longitudinal analysis on the repeated measures from each subject using logistic mixed effects models with a subject-specific random intercept. In each model, we will include time as a 4-level categorical predictor (with baseline serving as the reference level) as well as a treatment indicator and time-by-treatment interaction. We will jointly test the interaction coefficients to determine if the effect of treatment varies over time. If the effect is found to vary over time, we will test the intervention effect at each time point and characterize the difference between the treatment and control groups using risk differences and their corresponding 95% CIs. If no evidence of a time-by-treatment interaction is present, we will refit the logistic model without the interaction terms and provide the overall intervention effect and its corresponding 95% CI.

Furthermore, we will provide a descriptive analysis of each secondary outcome overall and within each intervention arm at each time point. Secondary outcomes will also be compared between the treatment and control groups using one-tailed *t* tests for continuous measures and chi-square tests for categorical measures. The corresponding group differences (in mean scores or proportions) and their 95% CIs will be reported. Within the intervention group, we will investigate game use changes over time and whether there exists a dose-response relationship between various game use indicators (eg, amount of time playing the game) and the various survey responses, including HIV testing, intent to test for HIV, PrEP uptake, and intent to seek PrEP as well as the other secondary outcomes. Qualitative data from IDIs will be transcribed and involve thematic coding using Atlas.ti version 7.0 to identify themes regarding intervention delivery and acceptability.

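### Continuous secondary scales with a baseline measurement are compared by t tests that do not adjust for it, which costs precision and leaves the result exposed to chance baseline imbalance

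*Protocol article*

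**What the plan says.** The Secondary Outcomes section introduces its list after intent to test with "Other secondary outcomes will use previously published questions and validated scales (Table 1) and include changes in" HIV knowledge, risk perception and behaviors, PrEP knowledge, screening and uptake, risk estimator scores and locator use, and game acceptability and usability.

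The Measures section gives the survey schedule: "Electronic surveys via REDCap will be used to assess the behavior at baseline and at 1, 3, and 6 months post enrollment". HIV and PrEP knowledge and self-perceived risk are among the survey domains. The Overview of the randomized trial describes the baseline survey before it describes randomization, so these scores are genuine pre-randomization covariates.

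The Statistical Analysis section names the comparison: "Secondary outcomes will also be compared between the treatment and control groups using one-tailed *t* tests for continuous measures and chi-square tests for categorical measures". It names the estimate as well: "The corresponding group differences (in mean scores or proportions) and their 95% CIs will be reported". No covariate is mentioned. The only model in the article that uses baseline data is the "longitudinal analysis on the repeated measures from each subject using logistic mixed effects models with a subject-specific random intercept", which suits binary outcomes and not continuous scores.

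**The concern.** The plan collects a baseline value for each scale and names a between-arm test that makes no adjustment for it. It also leaves two candidate analysis variables. Secondary Outcomes speaks of changes, while Statistical Analysis speaks of differences in mean scores.

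These are different estimators. If one arm happens to start higher, the follow-up comparison drifts in that arm's favor and the change comparison usually drifts against it. If the choice is not fixed, it could be made after the data are seen.

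The scales matter to the trial's argument. The Theoretical Framework section expects the game to act through HIV risk perception, HIV and PrEP knowledge and self-efficacy. The sample size was set for HIV testing, and no power or SD is given for any continuous scale, so precision lost here is not covered by a planned reserve.

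**Working it through.** **The plan's own figure.** The article states that "A sample of approximately 300 subjects (150 per arm) would achieve >80% power to detect a moderate effect", namely 10% against 23% ("equivalent to a relative risk of 2.3 assuming a 10% prevalence of HIV testing in the past 4-6 months in the control group"), "using a two-sided test at a 5% significance level and assuming a 16% attrition rate after 6 months". Completers: 300 × 0.84 = 252, or 126 per arm. Power at 126 per arm is 79.8% (pooled variance), 80.6% (unpooled) or 80.9% (arcsine), and the pooled formula needs 303 in total. The stated figure therefore reproduces to within rounding. It concerns the primary outcome only, and it supplies the 126 per arm used below.

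**Assumptions for the scales.** The correlation r between baseline and follow-up is not in the documents, so 0.3, 0.5 and 0.7 are assumed. The SD is assumed equal at both times, and the outcome variance is set to 1.

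**Variance per participant**
- t test on the follow-up score: 1
- t test on the change: 2(1 − r)
- follow-up score adjusted for baseline: 1 − r²

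**Ratios to the adjusted analysis**
- change: 2(1 − r)/(1 − r²) = 2/(1 + r)
- follow-up only: 1/(1 − r²)

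| r | Change ÷ adjusted | Follow-up ÷ adjusted |
|---|---|---|
| 0.3 | 2/1.3 = 1.54 | 1/0.91 = 1.10 |
| 0.5 | 2/1.5 = 1.33 | 1/0.75 = 1.33 |
| 0.7 | 2/1.7 = 1.18 | 1/0.51 = 1.96 |

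Both ratios exceed 1 for every r strictly between 0 and 1. At r = 0.5, 252/1.333 = 189. Confidence intervals widen by the square root of each ratio: 24%, 15% and 8% for change, and 5%, 15% and 40% for follow-up only. The ratios do not depend on whether the test is one- or two-sided.

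**Detectable difference and power.** The detectable difference in SD units is (1.96 + 0.84) × √(2v/126), where v is the variance per participant (126 per arm, 80% power, two-sided 5%). Power is for a true difference of 0.353 SD. Each cell gives follow-up / change / adjusted.

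| r | Detectable difference (SD) | Power at 0.353 SD |
|---|---|---|
| 0.3 | 0.353 / 0.418 / 0.337 | 80% / 66% / 84% |
| 0.5 | 0.353 / 0.353 / 0.306 | 80% / 80% / 90% |
| 0.7 | 0.353 / 0.273 / 0.252 | 80% / 95% / 97.5% |

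**Chance imbalance.** The SD of the baseline difference between arms is √(2/126) = 0.126 SD units. An imbalance of that size shifts the follow-up comparison by r × 0.126 and the change comparison by (r − 1) × 0.126:
- r = 0.3: +0.038 and −0.088
- r = 0.5: +0.063 and −0.063
- r = 0.7: +0.088 and −0.038

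In a simulation of 20,000 trials per r, the correlation of the follow-up, change and adjusted estimates with the chance baseline difference was +0.30, −0.59 and 0.00 at r = 0.3. It was +0.51, −0.49 and 0.01 at 0.5, and +0.70, −0.39 and 0.00 at 0.7. Averaged over trials, all three estimates recovered the true difference.

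**The case against.** The strongest reply is that nothing here is wrong. Under 1:1 stratified randomization both t tests are valid, only secondary outcomes are touched, and no stated precision target is missed. An article often leaves covariate adjustment to its analysis plan. All of this stands except the last step: the article names a method for these outcomes, and an analysis plan that follows it would inherit that method.

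The size of the loss is also assumed. Under each reading it is small at one end of the range: 1.18 for change at r = 0.7, and 1.10 for follow-up only at r = 0.3. That stands too.

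A reader might infer several stronger points that the documents do not support.
- **That change scores are the fixed endpoint.** The reference to changes covers a list that includes game usability and reasons for stopping use, which have no pre-intervention value. The wording is loose and does not define the analysis variable.
- **That a change score over-corrects whenever r is below 1.** The right coefficient is r × SD(follow-up)/SD(baseline), so the statement needs equal SDs.
- **That knowledge scores sit near a ceiling.** No scale range or baseline mean is given.
- **That adjustment removes imbalance altogether.** It removes the linear effect of imbalance in that one baseline score.

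**Conclusion.** The point holds as a matter of efficiency. The named t tests are valid and unbiased on average, but under either reading they give a less precise estimate than the same data allow, and one that moves with chance baseline differences. With equal SDs and r from 0.3 to 0.7, the excess variance is 18% to 54% for change scores and 10% to 96% for follow-up scores alone. The direction holds for any r strictly between 0 and 1 under equal SDs. The size depends on an r that the documents do not give.

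The scope is continuous scales with a baseline, such as HIV knowledge, PrEP knowledge and perceived susceptibility. It does not extend to game acceptability, usability, play time or categorical items, and it has no bearing on the primary analysis. That the t tests are one-tailed, beside a two-sided primary test and 95% CIs, is a separate matter.

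**What to change.** In Statistical Analysis, for continuous secondary scales that have a baseline measurement, replace the t test with one of these:
- a linear regression of the 6-month score on arm, that scale's baseline score and the randomization strata (age group, sexual behavior); or
- a baseline-adjusted linear mixed model over the 1-, 3- and 6-month scores.

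Report the adjusted mean difference with its two-sided 95% CI, in line with the two-sided primary test. State the choice and the time point before trial data are available, and say which outcomes keep an unadjusted comparison because they have no baseline. With the baseline score in the model, the question of change or follow-up score also falls away, because both give the same adjusted treatment difference.

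The cost is analysis-plan wording and a little analysis work. No new data, visits or participants are needed.
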